### 11.3 Background and Demographic Characteristics

The background and demographic variables will be displayed in per subject listings. The quantitative variables will also be summarized by means, standard deviations and medians. The qualitative variables will be displayed in frequency tables.

### 11.4 Analysis of Efficacy Parameters

#### **Fatty acid analysis**

Serum concentrations of fatty acids will be reported for the child and mother and displayed in per subject listings and graphs. The efficacy parameters will be displayed in per subject listings and summarized by means, standard deviations and median values.

#### **ROP evaluation**

The ophthalmologic assessment will be performed with strict criteria according to general Swedish Guidelines issued by the Swedish Ophthalmological Society: The Guidelines are available at following link: [www.swedeye.org/SOTA/rop/SOTA-ROP\\_2006.pdf](http://www.swedeye.org/SOTA/rop/SOTA-ROP_2006.pdf).

The evaluation of ROP stage 3 or more will be assessed by retinal examination by a trained ophthalmologist and will be performed in a blinded fashion i.e. the ophthalmologist will be unaware of whether or not the infant is participating in the clinical study.

### 11.5 Analysis of Safety/Tolerability

Physical examination, MRI and the results of retinal examination will be displayed in per subject listing.

The vital signs and laboratory measurements will be listed per subject and illustrated graphically as levels per time-point (as per Table 1, page 11) by each subject. The measurements will also be summarized by descriptive statistics.

Adverse events will be displayed in per subject listings.

--- ❖ ---

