| Primary Study Objectives:  | 
A) The objective of this study is to determine how fatty acid (FA) levels in prematurely born children are affected by supplementation of “physiologic levels of long chain polyunsaturated fatty acids (LCPUFA) i.e. Omega-3 and 6
 
B) To determine whether these FA levels protect against development of retinopathy of prematurity (ROP)
                                                                                                                       |
| Secondary Study Objective: | 
C) To determine whether these FA levels normalize growth (length, weight, head circumference) and/or
 
D) To determine whether these FA levels reduce the risk of lung, brain and gut morbidity
                                                                                                                                                                                                                                                                     |
| Efficacy Endpoints:        | 
To compare in supplemented versus conventionally treated children
 
A) Serum and breast milk FA levels at days 1, 7, 14, 28 and in postmenstrual weeks 32, 36 and 40 and from breast milk FA levels day 7 and postmenstrual weeks 36 and 40.
 
B) Development of ROP
 
C) SDS score with regard to length, weight and head circumference growth.
 
D) Bronchopulmonary dysplasia, brain development on MRI examination and necrotizing enterocolitis
 |

**Safety Endpoints:** Adverse events, clinical chemistry, retinal exam, physical examination, vital signs.

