## **5 STUDY SUBJECTS**

### **5.1 Number of Subjects**

For efficacy evaluations, 80 subjects need to be included for statistical considerations. However, to compensate for protocol violations and withdrawals up to 90 subjects will be included (see **11.1 De-termination of Sample Size and Statistical Methods** on page 26).

After the first 20 subjects have been treated and evaluated there will be a safety check to confirm that the safety profile is acceptable and that the assumption of a 50% reduction in ROP incidence is reasonable. A second safety check will be performed after the next 20 subjects.

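### Section 11.5 assigns adverse events to per-subject listings and states no by-arm frequencies, although they are a named safety endpoint; brain MRI has a weaker form of the same gap

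*Protocol*

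**What the plan says.** **Endpoints.** The Protocol Synopsis gives the safety endpoints as "Adverse events, clinical chemistry, retinal exam, physical examination, vital signs". The efficacy endpoints open with "To compare in supplemented versus conventionally treated children", and item D under that line is "Bronchopulmonary dysplasia, brain development on MRI examination and necrotizing enterocolitis".

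**Analysis.** For adverse events, section 11.5 says "Adverse events will be displayed in per subject listings" and nothing more. On examinations it says "Physical examination, MRI and the results of retinal examination will be displayed in per subject listing". Vital signs and laboratory values are to be listed and graphed per subject, and then "The measurements will also be summarized by descriptive statistics".

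**Elsewhere in section 11.** Section 11.1 tests ROP stage between arms with the Mann-Whitney test and models weight, length and head circumference with treatment as a fixed factor. Section 11.3 gives qualitative baseline variables both listings and frequency tables. Section 11.4, under the fatty acid heading, says "The efficacy parameters will be displayed in per subject listings and summarized by means, standard deviations and median values".

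**The concern.** A per-subject listing is useful for reviewing cases, but it does not show whether one arm has more events than the other. That matters here for three reasons.

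- **Background events.** Section 1 describes preterm birth as strongly associated with morbidity in several organ systems. Many infants in both arms can be expected to have events whichever emulsion they receive. Randomisation separates an emulsion effect from that background only if events are counted by arm.
- **Causality assessment.** Under section 9.1 an event counts as related only if, among other conditions, the infant's clinical state cannot reasonably explain it. In this population clinical state can explain a great deal, so case-by-case attribution is a weak signal. The only blinding described in section 6.3 is that of the ophthalmologic assessment.
- **Prior safety evidence.** The two earlier studies of the test emulsion cited in section 1 enrolled infants below 32 weeks, and infants of at most 34 weeks weighing 1000 to 2500 g. Both used a soybean oil emulsion as comparator, not Clinoleic, so this trial's own comparison is needed.

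At stake is a prespecified comparison on a named safety endpoint. If by-arm tables are chosen only after the data are seen, the choice of events and groupings is post hoc.

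**Working it through.** The protocol states no figure for adverse events or MRI, so there is nothing of its own to reproduce. Its one power calculation concerns ROP and does not bear on this point. The check is mainly a reading of the text.

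**Step 1. Role of each variable against its stated analysis.**

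| Variable | Role in Synopsis | Analysis stated in section 11 |
|---|---|---|
| Adverse events | Safety endpoint | Listing (11.5) |
| Vital signs, laboratory | Safety endpoint | Listing, graph and descriptive summary (11.5) |
| Retinal examination / ROP | Safety and efficacy endpoint | Listing (11.5) and Mann-Whitney test by arm (11.1) |
| Growth | Efficacy endpoint C | Mixed model with treatment (11.1) |
| Brain MRI | Efficacy endpoint D | Listing (11.5); possibly the general sentence in 11.4 |
| Qualitative baseline variables | Not an endpoint | Listing and frequency tables (11.3) |

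**Step 2. Adverse events.** Section 11.5 adds a summary for vital signs and laboratory values with the word *also*, and section 11.3 adds frequency tables for baseline categories. The authors therefore treat a listing and a summary as different outputs. Adverse events receive only the first, and no other text in section 11 mentions them. The contrast shows that no summary is stated; it does not show that laboratory values are compared, because that sentence names no arms either.

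**Step 3. MRI.** The only between-arm analyses in section 11 are those of ROP and growth. The general sentence in 11.4 could be read to cover MRI as an efficacy parameter. It stands under the fatty acid heading, mentions no arms, and offers means, standard deviations and medians, which suit MRI findings poorly.

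**Step 4. What a by-arm table would add (assumed counts, 45 per arm as in the Synopsis).**

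- Suppose 12/45 infants in one arm and 4/45 in the other have a given event. The difference is 0.2667 − 0.0889 = 0.178.
- Standard error = √(0.2667 × 0.7333/45 + 0.0889 × 0.9111/45) = 0.0784.
- 95% CI = 0.178 ± 1.96 × 0.0784 = 0.024 to 0.331, that is, 2.4 to 33.1 percentage points.
- With the same assumed rate p in both arms, the CI half-width is 1.96 × √(2p(1 − p)/45). This gives 12.4 points at p = 10%, 16.5 at 20%, 18.9 at 30% and 20.7 at 50%.

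These figures show the precision that a table would make visible. They are not predictions for this trial.

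**Step 5. Are the data there?** Section 9.1 already requires term, dates, severity, seriousness, outcome (including death) and causality for each event. Section 8.2 requires MRI deviations from normal to be described on the CRF.

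**The case against.** **The protocol never says listings only.** This is true. The sentence that lists MRI also lists the retinal examination, and retinal outcome is compared by arm in section 11.1, so a listing in 11.5 does not by itself rule out an analysis elsewhere. For adverse events, however, there is no analysis elsewhere in section 11, and the contrast with vital signs and laboratory values stands.

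**MRI has two roles.** Section 8.2 also makes it a safety evaluation, and a listing of deviations is a natural output for that role. Its efficacy role may fall under the general sentence in 11.4. This has weight, and it is why MRI is the secondary point. What remains is that an endpoint defined as a comparison has no stated comparison.

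**Adverse event tables belong in a statistical analysis plan.** Detailed layouts often do, and a plan that is not shown may contain them. But section 11.5 is not silent: it states a method that falls short of what a named endpoint needs. The finding concerns that statement.

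**Stronger readings.** A reader might infer that the trial could not conclude on safety at all. The text does not support this: laboratory values and vital signs are summarised, event data are recorded in full, and nothing prevents later tabulation. A reader might also infer that the two safety checks in section 5.1, meant "to confirm that the safety profile is acceptable", would have nothing comparative to judge. That section does not say what the checks review and does not tie them to 11.5.

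**Conclusion.** The point holds for adverse events. Followed as written, section 11.5 yields no frequency of adverse events by randomised arm, although adverse events are a named safety endpoint and the population's background morbidity makes the randomised comparison the informative one. For brain MRI it holds in a narrower form: no text in section 11 compares it between arms, although the Synopsis defines it as an endpoint for that purpose.

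The conclusion rests on reading 11.5 as the full stated presentation of adverse events, which the contrasts within 11.5 and with 11.3 support. It also rests on the expectation, in line with section 1, that background events are common. Its size cannot be taken from the protocol, and the figures above depend on assumed counts and rates. No data are lost and no stated figure is wrong, so this is a cheap improvement.

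**What to change.** In section 11.5, replace the adverse event sentence with a by-arm presentation:

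- Number and percentage of infants in each randomised arm with at least one adverse event, serious adverse event, related adverse event (stating whether possibly related events are included) and death.
- The same by adverse event term and by severity.
- Risk differences with 95% CIs for serious adverse events and deaths. An interval that behaves well at small counts, such as a score-based one, would be preferable to the simple Wald form used above for illustration.
- Per-subject listings kept as support.

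Add one sentence, in 11.4 or 11.5, providing a summary of brain MRI findings by arm, in a form that suits how the findings are recorded.

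The cost is a few extra tables from data already on the CRF, with no added sampling, visits or infants. With 45 per arm the intervals will be wide, and the text should present these tables as estimation and not as powered tests.

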## **APPENDIX I**

### **WORLD MEDICAL ASSOCIATION DECLARATION OF HELSINKI**

#### **Ethical Principles for Medical Research Involving Human Subjects**

Adopted by the 18th WMA General Assembly Helsinki, Finland, June 1964 and amended by the:

29th WMA General Assembly, Tokyo, Japan, October 1975

35th WMA General Assembly, Venice, Italy, October 1983

41st WMA General Assembly, Hong Kong, September 1989

48th WMA General Assembly, Somerset West, Republic of South Africa, October 1996

52nd WMA General Assembly, Edinburgh, Scotland, October 2000

#### **A. INTRODUCTION**

1. The World Medical Association has developed the Declaration of Helsinki as a statement of ethical principles to provide guidance to physicians and other participants in medical research involving human subjects. Medical research involving human subjects includes research on identifiable human material or identifiable data.
2. It is the duty of the physician to promote and safeguard the health of the people. The physician's knowledge and conscience are dedicated to the fulfillment of this duty.
3. The Declaration of Geneva of the World Medical Association binds the physician with the words, "The health of my subject will be my first consideration," and the International Code of Medical Ethics declares that, "A physician shall act only in the subject's interest when providing medical care which might have the effect of weakening the physical and mental condition of the subject."
4. Medical progress is based on research which ultimately must rest in part on experimentation involving human subjects.
5. In medical research on human subjects, considerations related to the well-being of the human subject should take precedence over the interests of science and society.
6. The primary purpose of medical research involving human subjects is to improve prophylactic, diagnostic and therapeutic procedures and the understanding of the aetiology and pathogenesis of disease. Even the best proven prophylactic, diagnostic, and therapeutic methods must continuously be challenged through research for their effectiveness, efficiency, accessibility and quality.
7. In current medical practice and in medical research, most prophylactic, diagnostic and therapeutic procedures involve risks and burdens.
8. Medical research is subject to ethical standards that promote respect for all human beings and protect their health and rights. Some research populations are vulnerable and need special protection. The particular needs of the economically and medically disadvantaged must be recognized. Special attention is also required for those who cannot give or refuse consent for themselves, for those who may be subject to giving consent under duress, for those who will not benefit personally from the research and for those for whom the research is combined with care.
9. Research Investigators should be aware of the ethical, legal and regulatory requirements for research on human subjects in their own countries as well as applicable international requirements. No national ethical, legal or regulatory

requirement should be allowed to reduce or eliminate any of the protections for human subjects set forth in this Declaration.

## **B. BASIC PRINCIPLES FOR ALL MEDICAL RESEARCH**

10. It is the duty of the physician in medical research to protect the life, health, privacy, and dignity of the human subject.
11. Medical research involving human subjects must conform to generally accepted scientific principles, be based on a thorough knowledge of the scientific literature, other relevant sources of information, and on adequate laboratory and, where appropriate, animal experimentation.
12. Appropriate caution must be exercised in the conduct of research which may affect the environment, and the welfare of animals used for research must be respected.
13. The design and performance of each experimental procedure involving human subjects should be clearly formulated in an experimental protocol. This protocol should be submitted for consideration, comment, guidance, and where appropriate, approval to a specially appointed ethical review committee, which must be independent of the investigator, the sponsor or any other kind of undue influence. This independent committee should be in conformity with the laws and regulations of the country in which the research experiment is performed. The committee has the right to monitor ongoing trials. The researcher has the obligation to provide monitoring information to the committee, especially any serious adverse events. The researcher should also submit to the committee, for review, information regarding funding, sponsors, institutional affiliations, other potential conflicts of interest and incentives for subjects.
14. The research protocol should always contain a statement of the ethical considerations involved and should indicate that there is compliance with the principles enunciated in this Declaration.
15. Medical research involving human subjects should be conducted only by scientifically qualified persons and under the supervision of a clinically competent medical person. The responsibility for the human subject must always rest with a medically qualified person and never rest on the subject of the research, even though the subject has given consent.
16. Every medical research project involving human subjects should be preceded by careful assessment of predictable risks and burdens in comparison with foreseeable benefits to the subject or to others. This does not preclude the participation of healthy volunteers in medical research. The design of all studies should be publicly available.
17. Physicians should abstain from engaging in research projects involving human subjects unless they are confident that the risks involved have been adequately assessed and can be satisfactorily managed. Physicians should cease any investigation if the risks are found to outweigh the potential benefits or if there is conclusive proof of positive and beneficial results.
18. Medical research involving human subjects should only be conducted if the importance of the objective outweighs the inherent risks and burdens to the subject. This is especially important when the human subjects are healthy volunteers.
19. Medical research is only justified if there is a reasonable likelihood that the populations in which the research is carried out stand to benefit from the results of the research.

20. The subjects must be volunteers and informed participants in the research project.
21. The right of research subjects to safeguard their integrity must always be respected. Every precaution should be taken to respect the privacy of the subject, the confidentiality of the subject's information and to minimize the impact of the study on the subject's physical and mental integrity and on the personality of the subject.
22. In any research on human beings, each potential subject must be adequately informed of the aims, methods, sources of funding, any possible conflicts of interest, institutional affiliations of the researcher, the anticipated benefits and potential risks of the study and the discomfort it may entail. The subject should be informed of the right to abstain from participation in the study or to withdraw consent to participate at any time without reprisal. After ensuring that the subject has understood the information, the physician should then obtain the subject's freely-given informed consent, preferably in writing. If the consent cannot be obtained in writing, the non-written consent must be formally documented and witnessed.
23. When obtaining informed consent for the research project the physician should be particularly cautious if the subject is in a dependent relationship with the physician or may consent under duress. In that case the informed consent should be obtained by a well-informed physician who is not engaged in the investigation and who is completely independent of this relationship.
24. For a research subject who is legally incompetent, physically or mentally incapable of giving consent or is a legally incompetent minor, the investigator must obtain informed consent from the legally authorized representative in accordance with applicable law. These groups should not be included in research unless the research is necessary to promote the health of the population represented and this research cannot instead be performed on legally competent persons.
25. When a subject deemed legally incompetent, such as a minor child, is able to give assent to decisions about participation in research, the investigator must obtain that assent in addition to the consent of the legally authorized representative.
26. Research on individuals from whom it is not possible to obtain consent, including proxy or advance consent, should be done only if the physical/mental condition that prevents obtaining informed consent is a necessary characteristic of the research population. The specific reasons for involving research subjects with a condition that renders them unable to give informed consent should be stated in the experimental protocol for consideration and approval of the review committee. The protocol should state that consent to remain in the research should be obtained as soon as possible from the individual or a legally authorized surrogate.
27. Both authors and publishers have ethical obligations. In publication of the results of research, the investigators are obliged to preserve the accuracy of the results. Negative as well as positive results should be published or otherwise publicly available. Sources of funding, institutional affiliations and any possible conflicts of interest should be declared in the publication. Reports of experimentation not in accordance with the principles laid down in this Declaration should not be accepted for publication.

**C. ADDITIONAL PRINCIPLES FOR MEDICAL RESEARCH COMBINED WITH MEDICAL CARE**

28. The physician may combine medical research with medical care, only to the extent that the research is justified by its potential prophylactic, diagnostic or therapeutic value. When medical research is combined with medical care, additional standards apply to protect the subjects who are research subjects.
29. The benefits, risks, burdens and effectiveness of a new method should be tested against those of the best current prophylactic, diagnostic, and therapeutic methods. This does not exclude the use of conventional fatty acid supplementation, or no treatment, in studies where no proven prophylactic, diagnostic or therapeutic method exists.
30. At the conclusion of the study, every subject entered into the study should be assured of access to the best proven prophylactic, diagnostic and therapeutic methods identified by the study.
31. The physician should fully inform the subject which aspects of the care are related to the research. The refusal of a subject to participate in a study must never interfere with the subject-physician relationship.
32. In the treatment of a subject, where proven prophylactic, diagnostic and therapeutic methods do not exist or have been ineffective, the physician, with informed consent from the subject, must be free to use unproven or new prophylactic, diagnostic and therapeutic measures, if in the physician's judgment it offers hope of saving life, re-establishing health or alleviating suffering. Where possible, these measures should be made the object of research, designed to evaluate their safety and efficacy. In all cases, new information should be recorded and, where appropriate, published. The other relevant guidelines of this Declaration should be followed.

[figure not shown]

